## Abstract

**Background:**

Induction therapy with IL-2 receptor antagonist (IL2-RA) is recommended as a first-line agent in low immunological risk kidney transplant recipients. However, the role of IL2-RA in the setting of tacrolimus-based immunosuppression has not been fully investigated.

**Aims:**

To compare different induction therapeutic strategies with 2 doses of basiliximab vs. no induction in low immunologic risk kidney transplant recipients as per KFSHRC protocol.

**Methods:**

Prospective, randomized, double blind, non-inferiority, controlled clinical trial

**Expected outcomes:**

1. Primary outcomes:

Biopsy-proven acute rejection within first year following transplant

2. Secondary outcomes:

a. Patient and graft survival at 1 year

b. eGFR at 6 months and at 12 months

c. Emergence of de novo donor-specific antibodies (DSAs)

**Trial registration:**

The study has been prospectively registered at clinicaltrials.gov (NTC: 04404127). Registered on 27 May 2020.

**Supplementary Information:**

The online version contains supplementary material available at 10.1186/s13063-021-05253-1.

## Introduction

The standard immunosuppression protocols for solid organ transplantation have evolved to permit reliable short-term graft survival, such that transplantation has become the preferred therapy for end-stage organ failure. In the case of renal transplantation, graft and patient survival exceed 90% during the first post-transplant year [1–3].

Two antibodies have been constructed and produced by recombinant DNA techniques from mouse myeloma cell lines: basiliximab, a chimeric monoclonal antibody which includes the entire murine variable region and is approximately 80% human, and daclizumab, a humanized monoclonal antibody which includes only the hypervariable murine component and is approximately 90% human [4–10]. Only basiliximab is currently on the market with the trade name of Simulect® (basiliximab, Novartis) while Zenapax® (daclizumab, Roche) was withdrawn from the market and have shown virtually the same results in phase III clinical trials, although a randomized, prospective, well-powered study between the two drugs using the currently recommended dosage schedules has not been performed [6, 9, 11–13].

Importantly, the phase II data established that serum basiliximab concentrations exceeding 0.2 μg/ml were sufficient to saturate CD25 on circulating T lymphocytes in vivo [14–16]. Interestingly, the phase II studies were carried out to determine the antibody dose during the first 4 to 6 weeks post-transplant which could achieve this concentration. This concentration can be achieved with single dose basiliximab, i.e., 20 mg [16, 17]. Clinical trials leading to the US FDA drug approval were mainly coupled with cyclosporin as main maintenance immunosuppressant drug. However, the use of basiliximab induction when combined with tacrolimus-based immunosuppression has not been thoroughly investigated in well-structured, randomized clinical trials [18].

### Aims

To compare different induction therapeutic strategies with basiliximab (2 doses vs. no induction, a placebo that is composed of 100 ml of normal saline) administered by primary, registered nurse in low immunologic risk kidney transplant recipients as per KFSHRC protocol (attached).

### Hypothesis

No induction is non-inferior to standard dose induction with basiliximab in low immunological risk kidney transplant recipients.

## Materials and methods

### Study design

The study is a prospective, randomized, double-blind controlled clinical trial to compare different induction therapeutic strategies in kidney transplant recipients. This study will enroll 70 subjects in each arm. Figure 1 presents a high-level overview of the study procedures. A schedule of assessments is provided in Appendix.

**Fig. 1 Fig1:**
[figure not shown]
Overview of study procedures

### Study settings

The potential participants will be screened at kidney transplant clinic at King Faisal Specialist Hospital and Research Centre (KFSHRC), Riyadh. KFSHRC is a tertiary referral hospital. It is consistently recognized as one of the nation’s top hospital specializing in Oncology, Organ Transplantation, Cardiovascular Diseases, Neurosciences and Genetic Diseases Potential candidates will be informed of the trial via formal meetings and trial information sheets. This study is reported in line with the Standard Protocol Items; Recommendations for Interventional Trials (SPIRIT) Statement.

### Recruitment

Patients will be recruited from kidney transplant clinic at King Faisal Specialist Hospital and Research Centre (KFSHRC). Involved practitioners will identify potentially suitable patients and, after providing them with information about the study, then will be offered to contact the research team. Upon contact by potential participants, a researcher will explain the study and assess them for study eligibility. If the potential participant remains interested in participating in the study, and after confirming eligibility, a signed consent form will be obtained.

### Study population

In order to be eligible to participate in this study, an individual must meet all the inclusion criteria and none of the exclusion criteria as described below.

#### Inclusion criteria

Male or female ≥18 yearsLiving donorLow immunological risk:
First (primary) transplant≤ 4 antigen mismatches (HLA A, B, DR, DQ matching scheme)Negative HLA Ab screening

#### Exclusion criteria

High immunological risk as per KFSHRC protocol including (see attached protocol for more details Additional file 1)HLA identical or zero mismatched transplantsReceiving cyclosporin as primary maintenance immunosuppressantHuman immunodeficiency virus (HIV) co-infectionPregnant or nursing femaleHas received an investigational medication within the past 30 daysHas a known contraindication to the administration of basiliximabSuspected or known to have a serious infectionMulti-organ transplant

### Randomization and blinding

After fulfilling the enrolment criteria and obtaining the informed consent, subjects will be randomized to receive either the standard therapy (Arm I) or placebo (no induction) (Arm II) with a 1:1 allocation, as specified in the intervention section below. A randomization algorithm has been generated by the statistician. The randomization algorithm will be maintained by the Department of Pharmacy and has been generated via the ralloc procedure in Stata™ (Jones and Kenward version 3.7.6), with block randomization: subjects will be divided into subgroups called blocks (block size: 8), such that the variability within blocks is less than the variability between blocks. Then, subjects within each block are randomly assigned to either group. The algorithm will be used to randomize patient following signing the informed consent and admission.

#### Blinding

The trial will be blinded with respect to basiliximab induction allocation. The study will be blinded to subjects and site study investigators, with the following exceptions:
A single pharmacistA single biostatistician

Blinding of the basiliximab induction is critical to the integrity of this clinical trial.

In case of an emergency, the principal investigator has the sole responsibility for determining if unblinding of a patient’s treatment assignment is warranted for medical management of the event. The patient safety must always be the first consideration in making such a determination. In other words, in the event of a medical emergency (unexpected serious adverse event) or pregnancy in an individual subject, in which knowledge of the basiliximab induction is deemed critical to the subject’s management, the blind for that subject may be broken by the treating physician.

Before breaking the blind of an individual subject’s blinded treatment, the investigator should have determined that the information is necessary, i.e., that it will alter the subject’s immediate management. The need to break the blind must first be discussed with the study investigators, and the best method to do this will be determined. Un-blinding would be restricted to the specific patient. It is the responsibility of the principal investigator to promptly document the decision and rationale for unblinding a document in the source documents.

#### Pregnancy

Women of childbearing potential (WOCBP) must be using an adequate method of contraception to avoid pregnancy throughout the study and for up to 8 weeks after the study in such a manner that the risk of pregnancy is minimized. WOCBP includes any female who has experienced menarche and who has not undergone successful surgical sterilization (hysterectomy, bilateral tubal ligation, or bilateral oophorectomy) or is not postmenopausal (defined as amenorrhea for 12 consecutive months; or women on hormone replacement therapy [HRT] with documented serum follicle stimulating hormone [FSH] level > 35 mIU/mL). Even women, who are using oral, implanted, or injectable contraceptive hormones or mechanical products such as an intrauterine device or barrier methods (diaphragm, condoms, spermicides) to pre-pregnancy or practicing abstinence or where the partner is sterile (e.g., vasectomy), should be considered to be of childbearing potential. WOCBP must have a negative serum pregnancy test (minimum sensitivity 25 IU/L or equivalent units of human chorionic gonadotropin [HCG]) within 72 h prior to the start of study medication. In case of pregnancy, the participant will withdraw from the study, and management will be differed to primary physician according the standard of care.

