### Interim analysis

The patients enrolled in the study will be monitored and interim data analysis will be performed at 6 months and 1 year. This will include: safety, acute rejection, antibody use for rejection, severe rejection, multiple rejections, efficacy failure, cause of graft loss, delayed graft function, study drug discontinuation, renal function and serious adverse events.

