## Treatment (interventions)

*Arm 1*: Two doses of basiliximab, 20 mg intravenously, at 0 and 4 days post engraftment. The first dose to be given prior to reperfusion*Arm 2*: No induction (i.e., 100 ml of normal saline) will be administered intravenously, at 0 and 4 days post engraftment.

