## Safety assessment

Safety and tolerability of the study medications including all side effects. Those will include any side effect that occurs upon initiation of therapy until 30 days after completion of therapy. An adverse effect is any untoward medical occurrence in a clinical investigation subject administered a medicinal product and which does not necessarily have a causal relationship with this treatment. An adverse effect can therefore be any unfavorable and unintended sign, symptom, or disease temporally associated with the use of a medicinal product, whether or not considered related to the medicinal product. Active ADR surveillance will be considered.

Adverse events and serious adverse events will be reported to KFSHRC Research Advisory Council and Saudi Food & Drug Authority, respectively, following their standard policies.

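### A participant who becomes pregnant is withdrawn from the study itself, although dosing ends at day 4 and the primary outcome runs to one year: a small, avoidable source of missing outcomes

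*Protocol article*

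**What the plan says.** The Pregnancy section (under Randomization and blinding) sets the rule: "In case of pregnancy, the participant will withdraw from the study". It then leaves her management to the primary physician. What she leaves is the study, not only study medication. The same section requires contraception throughout the study and a negative serum test "within 72 h prior to the start of study medication". Pregnancy at entry is an exclusion criterion.

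Treatment (interventions) gives the whole of the study treatment. Arm 1 is "Two doses of basiliximab, 20 mg intravenously, at 0 and 4 days post engraftment". Arm 2 is saline, which "will be administered intravenously, at 0 and 4 days post engraftment".

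Study end points makes biopsy-proven acute rejection in the first year the primary outcome. Patient and graft survival at one year is among the secondary outcomes. The Interim analysis section says "interim data analysis will be performed at 6 months and 1 year", and its list of contents includes rejection, graft loss and serious adverse events.

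Two sections touch on what happens to someone who leaves. Data collection and management asks that drop-out be documented. Duration of the study says that patients are followed under standard care. Neither says that trial outcomes are still collected after withdrawal.

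**The concern.** Withdrawal from the study cannot shorten an exposure that is already complete. What it can end is observation. As written, the rule takes a correctly randomised and fully dosed participant out of the study because of an event after randomisation, and the article provides no way to recover her later outcomes.

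At stake are missing primary outcomes that the protocol itself creates, in a non-inferiority comparison with few expected events. Counting an unobserved participant as free of rejection lowers her arm's rate; in the no-induction arm, that error favours non-inferiority. The protocol treats pregnancy during the trial as a real possibility, since the Blinding section names it as a ground for breaking the blind.

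**Working it through.** **Inputs.** From Statistical methods: historical rejection rate 1/16 = 0.0625; upper limit 0.15; margin 0.15 − 0.0625 = 0.0875; about 64 per arm, raised to 70 for losses. From Treatment (interventions): last dose at day 4. Assumed, because the documents give no figure: 0 to 3 pregnancies among 140 participants.

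1. **The plan's own figure.** n = z²·p(1−p)/d² with z = 1.96, p = 0.15 and d = 0.0875 gives 3.8416 × 0.1275 / 0.00765625 = 63.97, so 64. The stated figure is reproduced. The allowance for losses is 70 − 64 = 6 per arm, or 6/70 = 8.6%.

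2. **Participants affected.** 0/140 to 3/140 is 0% to 2.1%.

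3. **Expected events missed per withdrawal.** If her whole year went unobserved, the expected number is the one-year rate itself, 0.0625 to 0.15. A pregnancy found later in the year leaves less time in which to miss an event, so these are upper values.

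4. **Expected shift in an arm's rate per withdrawal.** 0.0625/70 = 0.09 percentage points, and 0.15/70 = 0.21 points. Against the 8.75-point margin this is 1.0% to 2.4%. If all three assumed pregnancies fell in one arm, the shift would be at most 3 × 0.09 = 0.27 to 3 × 0.21 = 0.64 points.

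5. **Shift if one rejection really is missed.** 1/70 = 1.43 points, which is 1.43/8.75 = 16% of the margin. At 6.25%, an arm of 70 expects 70 × 0.0625 = 4.4 rejections, so one is roughly a fifth of the arm's total.

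6. **Precision.** The 95% half-width at p = 0.15 is 1.96·√(0.1275/n):

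| Evaluable per arm | Half-width |
|---|---|
| 70 | 0.0836 |
| 67 | 0.0855 |
| 64 | 0.0875 |
| 63 | 0.0882 |

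Even three withdrawals in one arm stay inside the 0.0875 target. It is missed only when losses for all reasons exceed 6 in an arm.

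**The case against.** The strongest reply is that the loss of data is inferred. The rule does not say that recording stops, and no section removes such a participant from the analysis. Data are collected partly by chart review and from hospital systems, patients remain under standard care, and a full protocol or analysis plan may say how withdrawn participants are handled. This stands as far as certainty goes: loss is the plain reading, not a literal statement. It does not clear the sentence, because the rule is explicit, and an analysis plan cannot recover outcomes that were not collected.

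A reader might go further in four ways that the documents do not support.

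- **That her one-year outcomes are lost altogether.** Anything recorded before withdrawal still counts, and the planned Kaplan-Meier and Cox analyses use her time up to that point. Only a first event between the pregnancy and month 12 can be missed.
- **That all safety follow-up is lost.** The Safety assessment section covers "any side effect that occurs upon initiation of therapy until 30 days after completion of therapy". If therapy means the two infusions, that window closes at about day 34, and a later pregnancy costs no routine adverse-event data. What may be lost is the serious adverse events in the 6-month and 1-year reviews, and secondary outcomes such as infection and graft survival.
- **That each pregnancy costs 16% of the margin.** That figure needs an unobserved rejection on top of the pregnancy. The expected cost is 1.0% to 2.4% of the margin.
- **That the rule can have no rationale.** Contraception is required throughout, and the concomitant immunosuppression is fixed, with other agents prohibited. A pregnant participant no longer meets the first condition and may not meet the second. That could explain ending trial procedures. The article gives no reason why outcome recording should end too.

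**Conclusion.** The point holds in a limited form. The protocol withdraws a pregnant participant from the study when, almost always, no study treatment remains to be stopped, and it makes no provision for recording her later outcomes. That is avoidable missing data after randomisation.

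The expected effect is small: at most 0.09 to 0.21 percentage points on an arm's rejection rate per withdrawal, within the existing allowance of 6 losses per arm. A single missed rejection would matter more, at 1.4 points. These sizes rest on an assumed 0 to 3 pregnancies among 140, on the protocol's own rates of 6.25% to 15%, and on reading withdrawal as the end of data collection. The case for changing the sentence is that the loss serves no stated purpose and costs little to prevent, not that it threatens the trial's conclusion.

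**What to change.** Replace the withdrawal clause in the Pregnancy section with wording to this effect: a participant who becomes pregnant remains in follow-up to month 12, unless she withdraws consent, for biopsy-proven rejection, graft and patient survival, serious adverse events and other outcomes available from standard-of-care records, and is analysed in the arm to which she was randomised. Study-specific procedures need not continue. Measured GFR is one example, since the article does not say that it is part of standard care. Leave the statement that her physician manages her care as it is; nothing here bears on her treatment.

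The cost is one sentence and some chart review. Study-specific secondary measures may still be missing for these participants, and the report should say so.

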### Interim analysis

The patients enrolled in the study will be monitored and interim data analysis will be performed at 6 months and 1 year. This will include: safety, acute rejection, antibody use for rejection, severe rejection, multiple rejections, efficacy failure, cause of graft loss, delayed graft function, study drug discontinuation, renal function and serious adverse events.

### Duration of the study

One year. See Appendix: Schedule of Assessment. However, the patients will be followed as part of standard of care of kidney transplant recipients.

### Statistical methods

The sample size projection is based upon historical data from transplants in 2018 and for which at least 1 year of follow-up has been achieved. These number 16 subjects and from whom one suffered rejection within the year, i.e., a rate of 0.0625. A margin of non-inferiority is proposed such that the true rejection rate among those treated without Simulect® would not be more than 15%, i.e., a margin of 0.0875 (0.1500 minus 0.0625). We recruit patients for the study and calculate a 95% confidence interval for the true rejection rate among those treated without Simulect®. This confidence interval will be P ± SE(p). We wish that the confidence interval for the rate to be at least 0.0875. The standard error of p is SQRT(p(1-p)/n). Solving for *n* yields a value of approximately 64. Accounting for loss to follow-up and other logistical issues, we have added to this number. We propose that the sample size in each arm be 70 subjects.

Statistical analysis will be performed using SAS/JMP Version 14 (SAS Institute, Cary, NC). Baseline parametric data will be expressed as means of and standard deviations and any differences in the groups will be analyzed with the paired Student’s *t* test, the chi-square test, or the Mann-Whitney *U* test as appropriate. *P* values less than 0.05 will be considered statistically significant. Multivariate analysis will be used to adjust for other risk factors including the concomitant administration of other interacting medications such immunosuppressants. Kaplan-Meier survival analyses will be used to compare outcomes for patient survival, graft survival, rejection, and BK nephropathy. Univariate and multivariable stepwise. Cox regression analyses will be performed to determine risk factors associated with patient death, graft loss, and rejection. We will also use propensity score analyses as an additional means to account for group differences in baseline characteristics. A propensity score represents the likelihood of a patient receiving a particular treatment or, in this case, no basiliximab induction instead of two doses of basiliximab. Data analysis will be carried out after completion of therapy in retrospective manner.

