### Medication dosage and administration

A protocol was developed for immunosuppressive for renal transplant recipients. This protocol represents the overall knowledge, experience, and wisdom of the renal transplant team members according to the best available evidence but is not meant to substitute the general clinical judgment of transplant practitioners. All transplant team members are expected to follow this protocol and deviation from it is only allowed when clinically justified and after consultation with other team members. The 2016 September revision will be followed (Additional file 1).

The placebo is the solution for injection [i.e., 100 ml of normal saline] without basiliximab that is going to be prepared by the research team pharmacist.

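### The 15% ceiling and the 0.0875 margin are two different non-inferiority criteria unless the basiliximab rejection rate is exactly 6.25%, a figure that rests on one rejection in 16 patients

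*Protocol article*

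**What the plan says.** All of this is in the Statistical methods section of the protocol article. The planning rate comes from "historical data from transplants in 2018 and for which at least 1 year of follow-up has been achieved", and the section reports: "These number 16 subjects and from whom one suffered rejection within the year, i.e., a rate of 0.0625".

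Non-inferiority is then expressed in two ways within one sentence. The first is an absolute ceiling for one arm, that "the true rejection rate among those treated without Simulect® would not be more than 15" per cent. The second is a difference, "a margin of 0.0875 (0.1500 minus 0.0625").

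The interval that the section proposes belongs to the single-arm form: the investigators will "calculate a 95% confidence interval for the true rejection rate among those treated without Simulect". The margin becomes the precision target: "We wish that the confidence interval for the rate to be at least 0.0875". Solving for n gives about 64, raised to 70 per arm for losses. The Hypothesis section, by contrast, is comparative: no induction against standard-dose basiliximab.

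**The concern.** A non-inferiority margin says how much extra rejection is acceptable relative to basiliximab in this trial. Here it is what remains when a historical rate is subtracted from a ceiling. The ceiling and the remainder are presented as the same thing, which is true only if the concurrent basiliximab rate equals 6.25%. One event in 16 patients cannot establish that.

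If the basiliximab arm comes out lower, the 15% ceiling tolerates more excess rejection than 8.75 points. If it comes out higher, the ceiling tolerates less. A reader of the final report could then face a trial that passes on one criterion and fails on the other, with both traceable to the same sentence of the plan. The randomised basiliximab arm, the best evidence on the control rate, plays no part in the single-arm rule.

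**Working it through.** **Inputs (all from Statistical methods).** Historical rejections 1/16 = 0.0625; ceiling 0.15; margin 0.0875; 95% confidence; standard error √(p(1−p)/n); n about 64, then 70 per arm.

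**1. The plan's figure.** n = 1.96² × p(1−p) / w², with p = 0.15 and half-width w = 0.0875:

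n = 3.8415 × 0.1275 / 0.007656 = 63.97, so 64. The plan's figure reproduces. Other readings do not give it: p = 0.0625 gives 29.4, and plus or minus one standard error, as literally printed, gives 16.7 at p = 0.15. The historical rate therefore enters n only through the margin; the variance uses the ceiling.

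**2. Precision of 1/16.** Exact (Clopper-Pearson) limits: the lower solves 1 − (1−p)¹⁶ = 0.025, giving 0.0016. The upper solves (1−p)¹⁶ + 16p(1−p)¹⁵ = 0.025, giving 0.302. The interval, 0.2% to 30.2%, contains the 15% ceiling.

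**3. Sensitivity to one rejection among the 16.**

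| Rejections | Margin, ceiling held at 15% | n, ceiling held | Ceiling, margin held at 0.0875 | n, margin held |
|---|---|---|---|---|
| 0/16 | 0.1500 | 22 | 0.0875 | about 40 |
| 1/16 | 0.0875 | 64 | 0.1500 | 64 |
| 2/16 | 0.0250 | 784 | 0.2125 | about 84 |
| 3/16 | negative | none | – | – |

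With the ceiling held, n = 3.8415 × 0.1275 / margin². With the margin held, n = 3.8415 × c(1−c) / 0.0875², where c is the new ceiling.

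**4. Where the two criteria part.** The difference that the ceiling allows is 0.15 minus the basiliximab rate: 13 points at 2%, 8.75 at 6.25%, 5 at 10% and none at 15%.

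*Passes the ceiling, fails the margin.* 5/70 without induction, 0/70 with basiliximab.
- Single-arm Wald upper limit: 0.0714 + 1.96 × √(0.0714 × 0.9286 / 70) = 0.132, below 0.15.
- Between-arm Newcombe upper limit: d + √((u₁ − p₁)² + (p₂ − l₂)²). The Wilson limits are u₁ = 0.1566 for 5/70 and l₂ = 0 for 0/70, so the limit is 0.0714 + 0.0852 = 0.157, above 0.0875. A Wald interval for the difference gives 0.132, also above 0.0875, so the conflict does not depend on the interval chosen.

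*Fails the ceiling, passes the margin.* 8/70 without induction, 10/70 with basiliximab.
- Single-arm: 0.1143 + 1.96 × 0.0380 = 0.189, above 0.15.
- Between-arm Wald: −0.0286 + 1.96 × √(0.0380² + 0.0418²) = 0.082, below 0.0875.

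**5. Chance of success at 70 per arm.** Single-arm rule: the Wald upper limit is 0.132 at 5 events and 0.151 at 6, so success means at most 5 events, with chance P(X ≤ 5 | 70, p). Between-arm rule: sum the product of the two binomial probabilities over all outcome pairs whose 95% Wald upper limit for the difference is below 0.0875, with equal true rates.

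| True rate (both arms) | Single-arm, limit below 15% | Between-arm, limit below 0.0875 |
|---|---|---|
| 2% | 99.7% | 93% |
| 6.25% | 73% | 62% |
| 10% | 29% | 43% |
| 15% | 4% | 32% |

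The single-arm rule is the easier one at low rates and the harder one at high rates. They are different tests.

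**The case against.** Much of the case on the other side stands. The 15% ceiling is stated as a target in its own right, and the variance behind 64 uses that ceiling, so not everything hangs on 1/16. Under the single-arm rule the historical count does not enter the decision at all, and a 4% chance of success at a true no-induction rate of 15% is that rule working as intended. The single-arm chances also assume all 70 evaluable. The value 0.0875 is already a fixed number, and a journal article may leave its clinical rationale to the full protocol.

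Several stronger readings are tempting, and the document does not support them:

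- *One patient more or less moves n to 22 or 784.* It takes one rejection more or less, with the ceiling held. Changing only the number of patients gives about 71 (1/15) or 59 (1/17).
- *The 16 were selected for surviving a year, which lowers the rate.* The wording can equally mean that a year had elapsed since transplant. Nothing says that deaths or losses were dropped.
- *The 16 were not comparable with the trial population.* The article does not describe their eligibility or regimen. In a condensed article, that silence is not evidence.
- *Earlier charts are there to be used.* The Medication dosage and administration section says only: "The 2016 September revision will be followed". It gives no earlier transplant counts and no date of first use.

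What the objection does not answer is the conflict between the two criteria. Prespecifying 0.0875 does not help while the same sentence also fixes a 15% ceiling and the only interval described is for one arm.

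**Conclusion.** The concern holds as a defect in how the criterion is defined. The plan equates a single-arm ceiling of 15% with a between-arm margin of 8.75 points. They coincide only at a basiliximab rate of exactly 6.25%, which the historical data leave anywhere from 0.2% to 30.2%. The two can give opposite conclusions on plausible data, in either direction.

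The figures rest on these assumptions: the precision target is a half-width with z = 1.96 and p = 0.15 (the reading that reproduces 64); all 70 per arm are evaluable; the true rates are equal in both arms for the between-arm chances; and the intervals are Wald intervals, except where Newcombe is named. The values 22 and 784 show how fragile the derivation is with the ceiling held. They are not a range of sample sizes that the trial might need, and with the margin held the spread is only about 40 to 84. Nor do the documents show that the historical rate is biased or that the trial cannot succeed.

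**What to change.** In Statistical methods:

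1. State the margin once, as a fixed absolute difference in one-year biopsy-proven rejection (no induction minus basiliximab). For example, keep 0.0875, judged by the upper 95% limit of the difference against the concurrent basiliximab arm. Name the interval method.
2. Delete the derivation 0.1500 minus 0.0625 and the single-arm 15% criterion.
3. Print the exact 95% CI of 1/16 (0.2% to 30.2%) beside the planning rate. If further eligible historical patients are on record, use them to refine it.
4. Replace the single-value justification with the chance of concluding non-inferiority at 70 per arm over a range of control rates: with equal rates and a Wald interval, about 93%, 62%, 43% and 32% at 2%, 6.25%, 10% and 15%.

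The cost is rewording and a short calculation, and the restated chance of success at 70 per arm will look less favourable. The rewording itself adds no patients, but it may show that 70 is too few. As an illustration under assumptions that the article does not state (80% power, one-sided 0.025, 6.25% in both arms), a margin of 0.0875 needs (1.960 + 0.842)² × 2 × 0.0625 × 0.9375 / 0.0875² = 120.2, so 121 per arm. The investigators should either revisit the size or state openly what 70 per arm can deliver.
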